#### Safety evaluation

Safety is evaluated using vital signs, cardiopulmonary signs, adverse reactions, electrocardiography, and clinical laboratory tests (including liver and kidney functions and myocardium enzyme). These indices are compared before and after the drugs were taken.

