### Design

This clinical study was a randomized, double-blind, double control trial that tested drugs and placebo. Noninferiority (versus positive control) and superiority (versus placebo control) trials were conducted. Patients with positive tests for the influenza virus (rapid detection of antigens to the influenza virus before enrollment, but if detection of nucleic acid of the influenza virus or cultivation of the influenza virus was inconsistent, the patient was excluded) were assigned randomly into three groups of equal proportions (1:1:1). Groups were: oseltamivir treatment (positive control), BLG granule treatment (test group) and placebo group. Patients will accept 5-day treatment and 21-day observation. Patient follow-up was undertaken on days 1, 3, 5, 7, 21 (Table 1 and Figure 1). Specific items that were collected for each follow-up period are outlined in Table 1.

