#### Inclusion and exclusion criteria

Inclusion criteria are patients (i) with confirmed infection by the influenza A (H1N1, H3N2) or influenza B virus according to real-time polymerase chain reaction (PCR) or viral culture; (ii) aged 18 to 65 years; axillary temperature ≥38°C; at least two constitutional symptoms (headache, chill, myalgia or fatigue) and one respiratory symptom (cough, sore throat, or rhinitis) [30,31]; (iii) illness onset within 36 h; and (iv) granting of written informed consent. Exclusion criteria are detailed in Table 2.

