With regard to subgroup analyses, depending on the circumstances, factors that cannot be excluded may have an effect on the prognosis.

For safety analyses, the prevalence of adverse events in the two groups will be compared using the Pearson’s χ^2^test, as well as listing and describing the events that occur during the trial. A description of laboratory test results before and after the test will be described as normal/abnormal changes, as well as the relationship between the abnormal changes and the test drug; these changes will be stated.

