## Discussion

Treatment effectiveness, safety assurance and patient affordability are the key factors for any drugs, including Western medicines and TCHMs. This projected clinical trial will provide evidence as to whether BLG granules are suitable and safe for treating and preventing seasonal influenza.

BLG seems to display a clinical effect during the early onset of illness. Our previous study showed that *IPRS*, clemastanin B and lignin, which are separated from *IIR*, have antiviral roles in the early infection stage of the influenza virus [24-26]. Accordingly, we defined the time of illness onset to be <36 hours. Unfortunately, this criterion made patient recruitment quite difficult. However, this design, which is based on a combination of traditional medical experience and modern pharmacological study, should allow us to discover the objective treatment effectiveness of BLG.

The safety of TCHM is attracting major attention. First, in our study, BLG granules are used only for 5 days in the acute phase, so that it may be safe for humans. Second, we evaluate the safety of BLG based on changes in liver and kidney function after treatment. In addition, western medicines used for treating influenza (such as oseltamivir, which sells for 283 RBM/box in China) is expensive for ‘developing’ countries. Hence, we need to explore new, safe and inexpensive anti-influenza medicine. BLG, which sells for 12.00 RBM/box in China, would be a good choice.

Furthermore, according to basic science studies, the active ingredient of *IIR* also exerts immune-modulating and anti-inflammation effects *in vitro* and *in vivo*. Polysaccharides from *IIR* can promote production of interleukin-2 and interferon-γ, as well as the proliferation of lymphocytes and macrophages in mice [33]. Also, indirubin and its derivatives can suppress the expression of several pro-inflammatory cytokines induced by influenza infection in human macrophages and alveolar epithelial cells [27]. Hence, an evidence-based clinical trial to evaluate the effectiveness of BLG in treating inflammation induced by influenza infection certainly has merit.

In summary, we have described the first clinical trial for treatment using a single herb against influenza A and B viruses in China. We will hold a large-scale clinical trial to comprehensively evaluate the effectiveness and safety of BLG against influenza infection based on the results of this pilot study.

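### Measured safety (vital signs, ECG, laboratory tests) is judged by change from before to after treatment in recovering influenza patients, with no between-arm comparison named for it

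*Protocol article*

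**What the plan says.** The Safety evaluation section lists the measures: "Safety is evaluated using vital signs, cardiopulmonary signs, adverse reactions, electrocardiography, and clinical laboratory tests". It then gives the comparison for them: "These indices are compared before and after the drugs were taken".

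The safety paragraph of Statistical analyses treats two kinds of data differently. For adverse events it plans a group test: "the prevalence of adverse events in the two groups will be compared using the Pearson’s χ^2^test". For laboratory results it plans only a description: "A description of laboratory test results before and after the test will be described as normal/abnormal changes". Any link of such changes to treatment is to be reported, with no contrast against another arm. The Discussion uses the same language: "we evaluate the safety of BLG based on changes in liver and kidney function after treatment".

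The Design section sets three arms in equal proportions: "oseltamivir treatment (positive control), BLG granule treatment (test group) and placebo group". Patients enter while acutely ill; the entry criteria include "axillary temperature ≥38°C; at least two constitutional symptoms" and onset no more than 36 h earlier. Table 1 marks vital signs, ECG and laboratory inspection as mandatory at Visit 0 and again at Visit 3 (Day 7 + 1).

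**The concern.** A before-after difference isolates a drug effect only if the measure would otherwise have stayed still. Here it would not be expected to. Everyone is febrile and symptomatic at the first measurement, and the second comes after a 5-day treatment course. Fever is an entry condition, and its resolution is a primary outcome, so the vital signs are set up to change. Selecting patients on a temperature threshold adds regression to the mean. For enzymes, Table 3 of the article treats rapidly rising creatine kinase and CK-MB as a mark of severe illness, so the article itself links the course of illness to laboratory values.

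Two errors can follow. A rise caused by BLG can be offset by recovery and reported as little change, or a shift due to recovery can be read as an effect of BLG. The randomised placebo arm removes the shared illness course, but the article does not say that it will be used for these measures. Safety is half of the stated study aim, so the comparison matters.

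**Working it through.** The article gives no effect size, SD or expected change for any safety measure, so there is no plan figure to reproduce. The check is of what each comparison estimates, followed by an illustration under assumed shifts.

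**Inputs from the article**
- 177 patients (Number of participants and specimen collection), allocated 1:1:1 (Design): 177 / 3 = 59 per arm.
- Two-sided tests at 0.05 and 95% CIs (Statistical analyses).
- Mandatory safety measurements at Visit 0 and Visit 3 (Table 1).

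**Assumptions, not in the article**
- Recovery drift r and drug effect b, in units of the SD of within-patient change.
- All 59 patients per arm measured at both visits.

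**What each comparison estimates**
- Before-after change in the BLG arm: r + b.
- Before-after change in the placebo arm: r.
- BLG minus placebo: (r + b) − r = b.

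With r = −0.3 and b = +0.3, the BLG before-after change has expectation −0.3 + 0.3 = 0, while the between-arm contrast has expectation 0.3.

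**Normal/abnormal tables.** Group means cancel in this way; counts of individual crossings do not. The tables still carry the same confounding. A value raised by influenza at entry and kept raised by the drug is tabulated as abnormal both times, that is, no change. A normal-to-abnormal shift may come from the illness alone. Only the frequency in a concurrent arm separates these.

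**Illustration: if a within-arm paired test were run, with no drug effect.** The article states no such test for safety. Noncentral t, 58 degrees of freedom, noncentrality r × √59 (for example 0.3 × 7.681 = 2.304):

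| Assumed drift r (SD of change) | Chance of a significant within-arm change |
|---|---|
| 0 | 5% |
| 0.1 | 12% |
| 0.2 | 33% |
| 0.3 | 62% |
| 0.5 | 97% |
| 0.8 | about 100% |

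The BLG-versus-placebo comparison of change stays at 5% in every row, because equal drift cancels.

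**What the between-arm contrast can deliver at 59 v 59**
- Standard error of the difference in mean change: √(2/59) = 0.184 SD.
- 95% CI half-width: 1.98 × 0.184 = 0.36 SD.
- Power for b = 0.3: noncentrality 0.3 / 0.184 = 1.63, power about 37%.
- Power for b = 0.5: noncentrality 0.5 / 0.184 = 2.72, power about 77% (the normal approximation gives 78%).

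**The case against.** Four points can be made for the plan.

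1. **Adverse events already give a concurrent comparison.** Evaluation of adverse events defines an event to include adverse changes in vital signs and laboratory indices, and the prevalence of events is compared between groups. A reader might infer that measured safety has no between-group comparison at all; the documents do not support that. This point stands and narrows the gap to measured values and shifts not recorded as events. The protection is also loosely worded, since the sentence speaks of two groups in a three-arm trial without saying which.

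2. **No within-arm test is stated.** Laboratory results are to be described. A reader might infer that the plan carries a false-positive rate such as 62% or 97%. It does not: those figures belong to an unspecified test and an assumed drift. This point stands, so the table above is illustration only. Masking affects a descriptive table as well.

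3. **Before-after wording does not forbid setting changes side by side by arm, and fuller documents may do so.** The sentence in Safety evaluation is loose: it covers adverse reactions too, which are elsewhere compared between groups. This stands in part. However, the article does more than stay silent. It names a comparison in three places, and in one paragraph it gives adverse events a group test and laboratory results only a before-after description.

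4. **Entry criteria limit gross abnormality at baseline.** Table 2 excludes liver enzymes at or above three times the upper limit, creatinine above 2 mg/dL and leukocytes above 10.0 × 10^9/L. This helps for those tests, but milder illness-related deviations, and all vital signs, remain free to move.

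**Conclusion.** The concern holds in a limited form. For vital signs, ECG and laboratory measures, the comparison that the article names mixes recovery from influenza with any effect of BLG, and it leaves the randomised placebo arm unused for measured values and shifts not recorded as adverse events.

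The Discussion sentence might be taken to mean that the whole BLG safety conclusion rests on before-after change. It does not show that: it is one sentence on liver and kidney function, and adverse events form a separate, group-compared part of the evaluation.

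The size cannot be fixed from the documents. They give neither the amount nor the direction of recovery drift, so every SD shift above is an assumption. The structural conclusion needs only that some drift exists and that it is shared across arms when there is no drug effect. If a treatment itself changes the speed of recovery, the between-arm contrast estimates its net effect on the measure, which is still a randomised comparison.

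**What to change.** In Safety evaluation and in the safety paragraph of Statistical analyses:

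- Present before-after changes and normal/abnormal shift tables by arm, as description only.
- Add between-arm comparisons in the safety analysis population, BLG versus placebo and BLG versus oseltamivir. Compare Day 7 values adjusted for the Visit 0 value, and the proportion shifting from normal to abnormal. Give each with an estimate and 95% CI.
- State which arms the adverse-event comparison covers.

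No new data are needed, because Table 1 already requires the measurements at Visit 0 and Visit 3. The cost is a little more analysis. Precision is modest (a half-width of about 0.36 SD of change at 59 per arm, before any gain from baseline adjustment), so the text should say that an interval including zero is not evidence of no harm.

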#### Evaluation of adverse events

An adverse event refers to any adverse, unintended or unplanned effects on vital signs, symptoms, diseases, or laboratory indices that change after participants have enrolled in the clinical trial. An adverse event is not necessarily related to the drugs. Adverse events are divided into three levels: mild, moderate and severe (Table 4). The cause-and-effect relationship between an adverse event and study drugs is evaluated according to whether the agent (i) causes death; (ii) imperils life; (iii) leads to hospitalization or extends the duration of the hospital stay; (iv) is teratogenic or causes birth defects; (v) causes a permanent handicap; or (vi) is carcinogenic (Table 5). All serious adverse events must be reported within 24 h to the State Food and Drug Administration as well as the ethics committee.

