**Table 5 Tab5:** **Classification of adverse events**

**Classification**	**Feature**
**1. Definite**	Use of the experimental drug has a definite relationship with time.
	Similar pharmacologic effects of the drug or experimental drug are well known.
	There is no other plausible cause owing to disease or other explanations.
**2. Probable**	Use of the experimental drug has a reasonable relationship with time.
	Similar pharmacologic effects of the drug or experimental drug are well known.
	It is difficult to identify a cause owing to disease or other explanations.
**3. Possible**	Use of the experimental drug has a reasonable relationship with time.
	The adverse event may be caused by disease or other explanations.
**4. Remote**	There is a connection between time and test drug.
	It is easy to explain through disease or the main causes of a disease.
**5. Unrelated**	There is no connection between time and the test drug.
	The adverse event is definitely caused by other reasons, and not the test drug.

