##### Safety analysis population

For the safety analysis population, data will demonstrate efficacy after intervention for those patients who use the test drug at least once during randomization. In this study, the baseline data, MITT analyses and main indicators for treatment are employed in PP analyses, but the conclusion from MITT analyses is also evaluated. When undertaking PP analyses, if there are missing data, the last observation carried forward (LOCF) approach will be adopted to complete the dataset. For laboratory data, adverse events and side effects, we will use SA analyses, and the SAP will be the denominator for the prevalence of adverse reactions.

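### The causality sentence lists seriousness-type outcomes and conflicts with Table 5, so the relatedness rule is contradictory and serious adverse event has no definition

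*Protocol article*

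**What the plan says.** The section Evaluation of adverse events defines an adverse event broadly, notes that it need not be drug-related, and refers to Table 4 for three grades of severity. It then gives the rule for causality: "The cause-and-effect relationship between an adverse event and study drugs is evaluated according to whether the agent (i) causes death; (ii) imperils life". Four further items follow: new or longer hospitalization, birth defects, permanent handicap and cancer. The sentence closes with "causes a permanent handicap; or (vi) is carcinogenic (Table 5", so it presents Table 5 as the instrument for the same judgement.

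Table 5 has five levels, from definite to unrelated, and rests on other grounds. The criteria for the top level are "Use of the experimental drug has a definite relationship with time", "Similar pharmacologic effects of the drug or experimental drug are well known" and "There is no other plausible cause owing to disease or other explanations". The bottom level includes "The adverse event is definitely caused by other reasons, and not the test drug".

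The next sentence of the section sets a duty that depends on seriousness: "All serious adverse events must be reported within 24 h to the State Food and Drug Administration as well as the ethics committee".

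Adverse reactions are among the measures listed under Safety evaluation. The section Safety analysis population plans their rate: "the SAP will be the denominator for the prevalence of adverse reactions" (there, SAP means the safety analysis population).

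**The concern.** Death, a threat to life, hospitalization and the other three items are consequences of an event. They show how grave it was, not whether the study drug produced it. As a causality rule the list is also circular: asking whether the agent caused a death presupposes the answer it is meant to supply.

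Two things are at stake. The first is the adverse-reaction prevalence. A reaction differs from an event only in being attributed to the drug, so the numerator depends on the relatedness rule, and the article gives two rules that do not agree.

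The second is the meaning of *serious*. The only list that could define it is labelled as the causality test, and no other sentence supplies a definition. Three provisions use the word: the 24 h report, item 4 of the termination standards in Table 3, and the statement under Safety and ethics that moderate or serious events go to the ethics committee. That last statement also joins a severity grade from Table 4 to a seriousness term, although Table 4 has only mild, moderate and severe.

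**Working it through.** The article gives no adverse-reaction rate, expected or observed, so there is no figure to reproduce. The check sets the two rules side by side.

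| | Sentence in Evaluation of adverse events | Table 5 |
|---|---|---|
| Asks about | Gravity of the outcome | Timing, known pharmacology, other explanations |
| Yields | Yes or no on six outcomes | One of five relatedness grades |
| Shared criteria | None | None |

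**Step 1. Apply both rules to the same event.**

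- Mild nausea soon after a dose, with no other explanation. It meets none of the six items, so under the sentence it is not related. Table 5 allows a grade as high as definite if the effect is a known one.
- A liver-enzyme rise that leads to none of the six outcomes. The sentence again gives not related. Table 5 can grade it. The safety paragraph of Statistical analyses asks for the relationship of abnormal laboratory changes to the test drug to be stated, and for such a change only Table 5 can supply that.
- A hospitalization caused by influenza pneumonia. The six items ask what the agent does. An admission that the drug did not cause does not meet the hospitalization item, and Table 5 would place it low. The two rules need not differ here.

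The conflict therefore runs one way: the sentence drops non-serious drug reactions.

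**Step 2. Express the effect on the rate.** For one arm, let N be the size of its safety population, a the number of patients with at least one event that Table 5 attributes to the drug, and s the number of those a patients with an attributed event that also meets one of the six items. Assume that attribution of the serious events is the same under both rules.

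- Prevalence under Table 5: a/N
- Prevalence under the sentence: s/N, with s ≤ a
- Understatement: (a − s)/N

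The understatement is 0 if every affected patient has a serious reaction (s = a). It is the whole rate a/N if none does (s = 0). The article gives neither a nor s, so nothing narrower can be derived.

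**Step 3. Trace what depends on relatedness.** The adverse-reaction prevalence does, and so does the statement on laboratory changes. The Pearson χ² comparison in Statistical analyses does not: it is on adverse events, whatever their cause. Vital signs, electrocardiography and the normal/abnormal laboratory shifts are also reported without a relatedness grade.

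**The case against.** The strongest reply is that Table 5 is cited in the very sentence at issue and is the only instrument in the article that produces a relatedness grade. An assessor who has to enter a grade can get one only there. The list stands directly before the 24 h sentence, so a clause misplaced when the protocol was condensed is a natural explanation, and the full protocol or CRF instructions may define *serious* properly.

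Much of this stands. It makes correct grading in practice plausible, and nothing in the article shows that assessors used the list. It does not remove the error. The article does not leave the rule out; it states one, and that rule disagrees with its own table. Table 5 is headed only as a classification of adverse events, so it is the faulty sentence that tells the reader what the table is for.

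Some stronger conclusions are tempting and are not supported:

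- A reader might infer that causality and seriousness have been exchanged throughout. They have not: nowhere are causality criteria used to define seriousness.
- A reader might infer that hospitalizations due to influenza would be counted as drug reactions. The items ask what the agent leads to, so this does not follow.
- A reader might infer that the safety result for BLG (Ban-Lan-Gen) must come out near zero. The between-group test uses all adverse events, and only the adverse-reaction rate is exposed, on the condition that the sentence is followed.

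Which Table 5 grades count as a reaction is commonly left to the analysis plan and is not criticised here.

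**Conclusion.** The point holds as a contradiction between text and table. The stated causality rule consists of seriousness-type outcomes and cannot be reconciled with Table 5. If assessors follow the sentence, non-serious drug reactions are not counted as related and the adverse-reaction prevalence is understated. If they follow Table 5, the rate is sound and only the wording is wrong. The article does not show which happened, and the size of any misclassification cannot be derived from it.

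Independently of that, *serious* has no stated definition in the article, although expedited reporting, a termination standard and ethics committee reporting rely on it. The primary and secondary outcomes, the randomization and the planned comparison of adverse events are not affected. Since Study aims names safety alongside efficacy, and the correction is nearly free, it should be made.

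**What to change.** - In Evaluation of adverse events, state that relationship to study drug is graded only by Table 5, and give Table 5 a title that says so.
- Attach the six-item list to the definition of a serious adverse event, as the trigger for the 24 h report.
- Reconcile item 4 of Table 3 and the ethics committee sentence in Safety and ethics with that definition and with the severity grades of Table 4. Which events should end a patient's participation is a clinical decision outside this point.
- Check under blinding whether events already recorded were graded by Table 5, and re-grade any that were not. Trial status reports 50 patients finished by June 2014 out of 177 planned, so 177 − 50 = 127 were still to complete at that date.

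The cost is a small change to the wording and the CRF instructions, plus the blinded check. The reported adverse-reaction rate may turn out higher than it would under the sentence as written.
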